## Abstract

**Background/Objectives:** Sepsis and septic shock are the most severe forms of infection. Due to the intensive cross-talk of the coagulation and immune system, coagulopathies regularly occur in sepsis. The International Society on Thrombosis and Hemostasis refers to these coagulation abnormalities as sepsis-induced coagulopathies (SICs). The presence of SICs can be assessed using the SIC score. In parallel, a score for “sepsis-associated coagulopathy” (SAC) was introduced that, in contrast to the SIC score, allows coagulopathy to be classified according to its severity. In the past, multicenter, randomized controlled trials have repeatedly failed to prove the efficacy of specific therapeutic measures targeting SICs or SACs. This could potentially be explained by insufficient knowledge about the prevalence and incidence of SIC and the rate of spontaneous recovery. The Incidence of Sepsis-Induced Coagulopathy (INSIC) trial is intended to address this problem. **Methods:** The aim of the INSIC trial is to measure the incidence and prevalence of SIC—in addition to the rate of spontaneous SIC recoveries—during the first days of sepsis treatment to provide a solid base of data for future interventional trials. We aim to include all patients with sepsis treated in any one of 150 participating intensive care units in 100 hospitals located in Austria, Luxembourg, and Germany to determine the prevalence of SIC (on day 1 of the study period as well as on three selected days in the fourth quarter of each year from 2019 to 2024). SIC incidence will be assessed over a 14-day period starting on 10 March 2025. Secondary endpoints are 28-day survival and the occurrence of severe thromboembolic events and bleeding. In addition, each of the aforementioned outcome parameters will be assessed for correlation with the severity classification of the SAC score. **Conclusions:** The INSIC trial is the first study to determine the prevalence as well as the incidence of SIC, to prospectively examine the course of SIC longitudinally over a 14-day period, and to determine the rate of spontaneous recoveries within 72 h under standard treatment in a large cohort of patients. This information will provide a sound basis for future studies.

## 1. Introduction

Whenever wounds occur in nature, the human body relies on the simultaneous and rapid prevention of both further blood loss and the invasion of germs into the bloodstream. As a result, there is so much cross-talk between coagulation mediators and the innate immune response to infection that experts consider the two systems to be one [1]. The role of monocytes, neutrophil granulocytes, and the complement system are just three examples of this complicated cross-linking: activated monocytes express tissue factor (TF), factor III of the coagulation system. When neutrophil granulocytes are activated as part of the innate immune response, they eject, among other things, so-called neutrophil extracellular traps (NETs), in which bacteria become trapped and can then be cleared by phagocytes. These NETs activate factor XII of the coagulation cascade. Activated platelets in turn also activate the complement system and vice versa [1]. This seems evolutionarily useful as long as these interactions remain localized around wound areas. In the case of sepsis and septic shock, this intense cross-talk may become a problem. Defined as “life-threatening organ dysfunction caused by a dysregulated host response to infection”, sepsis and septic shock are the most severe forms of infection [2]. Coagulation disorders (coagulopathies) are an integral part of sepsis [3]. To address this phenomenon clinically, the International Society on Thrombosis and Hemostasis (ISTH) provided a screening tool for recognizing sepsis-induced coagulopathy (SIC) in 2017 named the SIC score [4] (Table 1). The aim of this tool is to detect SIC at an early stage before it develops into the severe form of overt disseminated intravascular coagulation (DIC) [4,5]. The latter occurs when a systematic, uncontrolled activation of coagulation leads to an excessive consumption of coagulation factors, resulting in deficiency and subsequent diffuse bleeding. Simultaneously, multiple microthrombi and thromboembolisms may occur. In order to describe different degrees of severity of coagulopathies in sepsis, almost simultaneously with the SIC score, the “sepsis-associated coagulopathy” (SAC) score (Table 1) was introduced, distinguishing “mild”, “moderate”, and “severe” SAC [6]. From a clinical perspective, it appears crucial to identify SIC at an early stage, as this is the only way to potentially intervene therapeutically and prevent obvious DIC with diffuse bleeding and thrombosis.

In a secondary analysis of two multicenter studies published in 2023, we were able to show that at least 20–25% of patients with sepsis or septic shock were affected by SIC, and that SIC was associated with increased morbidity as well as mortality [7,8,9]. However, the exact incidence of SIC is difficult to estimate, and the prevalence of SIC in retrospective studies varies from 20 to 80%, depending on the severity of the disease and the pre-selection of the respective study cohort [4,9,10,11]. This high level of variance makes a reliable calculation of expected case numbers for randomized controlled interventional trials (RCTs) extremely difficult [4,9,10,11]. This is most likely one of the main reasons why a number of RCTs that intended to modulate blood coagulation in sepsis therapeutically and thus to reduce sepsis mortality failed [12,13,14]. Most recently, an RCT investigating the effects of soluble recombinant thrombomodulin in patients with sepsis and SAC failed in 2019 because approximately 20% of the patients who had coagulopathy at the time of screening had experienced a spontaneous remission of SAC under standard sepsis therapy by the time the study drug was administered for the first time [14]. Nevertheless, coagulopathies in septic patients are strongly associated with increased morbidity and mortality [4,9,10], and addressing coagulopathies therapeutically may be a critical factor in reducing sepsis mortality.

The aim of this multicenter observational study is to measure the incidence of SIC and the rate of spontaneous SIC recovery in the first days of sepsis treatment, and thus to provide a solid foundation of data to inform further interventional RCTs.

### 1.1. Objectives

The primary outcome of the INSIC trial is the SIC incidence rate within a 14-day observation period (new cases/1000 ICU days). Moreover, we aim to determine the point prevalence of SIC on day 1 of the study period and on three reference days in the fourth quarter of each year from 2019 to 2023. The secondary outcome parameters are as follows: (I) length of stay in intensive care unit (ICU) until transfer to a normal ward; (II) ICU mortality rate (in all patients and in subgroups of patients with sepsis, septic shock, and SIC according to the different scores); (III) 28-day hospital mortality rate (in all patients and in subgroups of patients with sepsis, septic shock, and SIC according to the different scores); (IV) SIC recovery rate 72 h after SIC onset; (V) thromboembolic events after sepsis onset (in sepsis, septic shock, or SIC) up to day 28, death, or hospital discharge (whichever occurs first); and (VI) relevant bleeding without surgical trauma (non-trauma or surgery-related major bleeding causing a drop in hemoglobin of <1 g/dL) after the onset of sepsis (in sepsis, septic shock, or SIC) until day 28, death, or hospital discharge (whichever occurs first). (VII) Each of the above-mentioned outcome parameters will also be tested for correlation with the different degrees of severity of SAC (according to the SAC score) (Table 1), which allows for a more differentiated assessment of the severity of coagulopathy.

### 1.2. Trial Design

The INSIC trial is a combined retrospective and prospective, multicenter, international, cross-sectional, longitudinal and epidemiological observational study. This study protocol follows the standard protocol items in accordance with the Recommendations for Observational Trials (STROBE) guidelines.

## 2. Methods

### 2.1. Study Setting

The INSIC trial is a combined retrospective and prospective, multicenter, international, cross-sectional, longitudinal and epidemiological observational study. The aim of the study is to have 150 ICUs across 100 hospitals in Austria, Luxembourg, and Germany participate. The INSIC trial will be conducted by the network of the SepNet Critical Care Trials Group of the German Sepsis Foundation.

### 2.2. Eligibility Criteria

General patient data is collected from all adult patients treated in one of the participating intensive care units during the observation period (see Section 2.5). Patients are screened for sepsis on a daily basis. Patients are included in the detailed data collection if they fulfill all of the following criteria:The patient must be treated in a participating ICU.The patient must be ≥18 years of age.The patient must be diagnosed with sepsis or septic shock [2]:
Definition of sepsis: Acute suspected or confirmed infection plus a sepsis-induced increase in SOFA score by ≥2 points compared with baseline (last-documented value in the ICU or approximate baseline value in cases with known pre-existing conditions, e.g., documented SOFA impairment due to renal insufficiency, COPD, thrombocytopenia, or pre-existing brain damage). In cases where no pre-existing conditions are identified, the pre-existing SOFA score can be assumed to be “0”.Definition of septic shock: Sepsis plus persisting hypotension requiring vasopressors to maintain MAP ≥ 65 mm Hg plus lactate ≥ 2 mmol/L after an initial bolus volume of 30 mL/kg body weight (bw).

### 2.3. Interventions

There are no interventions.

### 2.4. Outcomes

The primary outcome parameters of the INSIC trial are as follows:
(1)The incidence rate of SIC within a 14-day observation period (new cases/1000 patient days).(2)The point prevalence of SIC on day 1 of the study period and on three reference days in the 4th quarter of each year from 2019 to 2023.

The secondary outcome parameters of the INSIC trial are as follows:
(1)Length of stay in the ICU until transfer to a normal ward.(2)ICU mortality rate (in all patients and in the subgroups of patients with sepsis, septic shock, SIC, or SAC (mild, moderate, severe) according to the different scores).(3)Mortality rate until day 28, hospital death, or hospital discharge (whatever occurs first, in all patients and in the subgroups of patients with sepsis, septic shock, SIC, or SAC (mild, moderate, severe) according to the different scores).(4)SIC and SAC (mild, moderate, severe) recovery rate 72 h after SIC or SAC onset. The time point was chosen as the 72 h period reflects a critical window during which early death in sepsis or a clinical response to sepsis therapy can be expected [15].(5)Thromboembolic events after sepsis onset (in sepsis, septic shock, SIC, or SAC (mild, moderate, severe)) up to day 28, death, or hospital discharge (whichever occurs first).(6)Relevant bleeding without surgical trauma (hemoglobin loss >1 g/dL within 24 h, due to bleeding rather than dilution) after sepsis onset (in sepsis, septic shock, SIC, or SAC (mild, moderate, severe)) until day 28, death, or hospital discharge (whichever occurs first).

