### 2.5. Procedure and Data Collection

We will collect general structural data (see Figure 1) for each participating study center. All patients treated in the participating ICUs in a 14-day period will be included. Notably, only data generated in the context of standard patient care will be collected. For each patient treated in the participating ICUs, the following data will be collected: gender, age, date and time of hospital admission, referring ward or hospital (if applicable), Simplified Acute Physiology Score (SAPS) II, date and time of hospital discharge, patient status at discharge (alive, dead, returning home, or going to a care facility). In addition, for each patient we intend to collect data describing the dates and times of ICU admission and discharge as well as the type of admission (surgery—planned or emergency; medical treatment—planned or emergency) and the survival status at ICU discharge.

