For each patient diagnosed with sepsis or septic shock during the observation period, more detailed information will be collected (date and time of sepsis onset, date and time of septic shock onset, infectious focus, causative pathogen(s), and secondary infections (super- and/or nosocomial infections and/or infections of a further organ system)). Furthermore, investigators will be asked to extract data from the hospital information system describing additional patient characteristics. These include the American Society of Anesthesiologists (ASA) classification [16], the Revised Cardiac Risk Index (RCRI) [17] score, the status of and, if applicable, the reason for pre-existing anticoagulation therapy or antiplatelet therapy, coagulopathy, and severe liver disease. Furthermore, information on past episodes of heparin-induced thrombocytopenia (HIT) type II will be collected. For all patients hospitalized with sepsis in the ICU on the first day of the observation period, it will be determined whether SIC was present before the start of the observation period. Furthermore, for each patient diagnosed with sepsis or septic shock during the observation period, on the day of sepsis diagnosis (day 0), on days 1–4, and on the day of sepsis discharge, the following measures will be collected: the sequential sepsis-related organ failure assessment (SOFA) score [2], the international normalized ratio (INR), and platelet count. For further exploratory analyses, the following parameters are recorded where available: anti-factor Xa activity, activated partial thromboplastin time (aPTT), prothrombin time, D-dimer level, fibrinogen concentration, thrombin–antithrombin complex (TAT) concentration, thrombin fragment F1.2 concentration, and measures from thrombelastometric testing. Likewise for exploratory analyses, the following parameters are collected: the levels of inflammation markers (C-reactive protein (CRP), procalcitonin (PCT), and interleukin-(IL) 6), as well as the dose of anticoagulant administered, the amount of fluid infused (per day), the amount of blood products transfused (per day), and the administered amount of coagulation factors and desmopressin (per day), determined at the same time points. Using the collected data and the SIC scores, all patients with sepsis will be tested for SIC at least once a day. Additionally, SIC scores (exact scores) will be recorded daily until day 14 after sepsis onset or discharge from the ICU (whatever occurs first). The date and time of the first SIC occurrence will be registered. The data collected will also be used to calculate the severity of SAC, according to Lyons et al. [6]. Finally, until day 14 after the onset of sepsis, each patient will be checked for thromboembolic events and non-trauma or surgery-related major bleeding (causing a drop in hemoglobin of <1 g/dL) once a day. In addition, on the 28th day after sepsis onset, it will be determined whether cardiovascular events, thromboembolic events, or non-trauma or surgery-related major bleeding (causing a drop in hemoglobin of <1 g/dL) occurred during the second 14 days of follow-up monitoring (yes/no recording for the second 14 days). Figure 2 provides an overview of the planned timeline. The time frames were chosen on the basis of balancing efforts and benefits. Since it is currently assumed that SIC occurs in the early phase of sepsis due to a dysregulation of the interaction of the innate immune response with the coagulation system, a special focus was placed on the first days, i.e., day 0 (sepsis onset) and the following 4 days. The aim is to identify possible early warning signs of SIC. Sepsis is usually treated anti-infectively for 7–14 days. The first occurrence of SIC after day 14 was considered very unlikely. The experts involved in the study planning were of the opinion that the occurrence of SIC after day 14 was most likely due to a secondary infection (which triggers a new sepsis episode) or another sepsis-independent reason. It was decided to use the 28-day mortality rate, as it is frequently collected in sepsis studies and thus allows an approximate comparison of the mortality of this cohort with other study cohorts. In the aforementioned effort to balance efforts and benefits, it was decided to investigate the potential effects of SIC on thromboembolism and bleeding risk up to day 28.

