### 2.18. Confidentiality

All collected data will be handled in accordance with the provisions of the General Data Protection Regulation (GDPR) of the European Union and the European Council [25]. All data containing the identity of the patient will only be accessible to the attending doctors and nursing staff; for all other investigators involved in the study, this data is encrypted and will use a pseudonym. Only the investigators at the respective study site are able to assign a pseudonym to a patient’s name, and only for as long as needed to complete data collection. After the 28-day follow-up, the data sets will be completely anonymized so that decryption is no longer possible. All data that will be processed and used in subsequent publications will be strictly anonymous.

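### ICU length of stay ends at an event that patients who die in the ICU never reach, so its comparison by SAC severity is at risk of bias

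*Protocol article*

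**What the plan says.** The outcome appears twice with the same end event: "length of stay in intensive care unit (ICU) until transfer to a normal ward" in Section 1.1 and "Length of stay in the ICU until transfer to a normal ward" in Section 2.4. Neither place mentions death. Other outcomes in the Section 2.4 list do have a stopping rule; the third, for example, is "Mortality rate until day 28, hospital death, or hospital discharge". Thromboembolic events and bleeding likewise stop at day 28, death or hospital discharge.

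Section 1.1, item VII, requires every listed outcome, ICU stay included, to be tested for correlation with SAC grade. Section 2.10 provides medians with interquartile ranges, Mann–Whitney or t-tests according to the type of variable, and Kaplan–Meier with log-rank for survival times. It names no competing-event method. The Introduction and Discussion both state that coagulopathy in sepsis goes with higher mortality.

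Section 2.5 collects ICU admission and discharge times for every patient, as well as "the survival status at ICU discharge".

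On the time limit, the ICU-mortality outcome reads "ICU mortality rate (in all patients and in the subgroups of patients with sepsis, septic shock, SIC, or SAC" and carries no horizon. Section 2.18 says sites can link pseudonym to patient "only for as long as needed to complete data collection", and then that "After the 28-day follow-up, the data sets will be completely anonymized so that decryption is no longer possible".

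**The concern.** An end event closed to patients who die leaves the analyst two obvious ways to apply the definition. One is to leave out ICU deaths, which compares survivors who were selected at different rates in the groups. The other is to let death end the stay, which turns an early death into a short stay. If severe SAC carries more deaths, both can make it look less demanding of ICU time than it is. Censoring at death removes that artefact, but it estimates stay as if nobody could die and hides the difference in deaths.

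The study is meant to supply planning data for interventional trials, so a misleading ICU-stay figure by coagulopathy grade could be carried into those designs. The primary incidence and prevalence outcomes are not affected.

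**Working it through.** **Planning figures.** They are not in dispute and only set the scale (Section 2.7: about 12,000 screened and 1500 septic patients in 4 weeks in 133 ICUs; here 14 days and 150 ICUs).
- ICU patients: 12,000 × 14/28 × 150/133 = 6767 (stated: around 6700).
- Septic patients: 1500 × 14/28 × 150/133 = 846 (stated: around 850).
- SIC: 30–60% of 850 = 255–510 (stated: around 250–500).

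**Illustration: inputs.** The protocol gives no ICU mortality and no discharge rate, so these are assumptions. The hazard of live discharge is d = 1/15 per day in both groups. ICU mortality m is 20% in the milder group and 40% in the more severe one. Hazards are constant.

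**Formulas.** From m = h/(h + d), the death hazard is h = d·m/(1 − m).
- Milder: h = (1/15)(0.2/0.8) = 1/60, total 1/15 + 1/60 = 1/12 per day.
- More severe: h = (1/15)(0.4/0.6) = 2/45, total 1/15 + 2/45 = 1/9 per day.

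**Median stay under each way of handling death.**

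| Handling of ICU death | Milder | More severe |
|---|---|---|
| Death ends the stay: ln 2 / total hazard | 12 × 0.693 = 8.3 days | 9 × 0.693 = 6.2 days |
| Deaths dropped, survivors only | 8.3 days | 6.2 days |
| Death censored: ln 2 / d | 15 × 0.693 = 10.4 days | 10.4 days |

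The first two rows agree because, with constant hazards, the time of leaving the ICU is independent of whether the patient leaves alive or dead. The rate of live discharge is identical in both groups, so the apparent 2.1-day difference comes entirely from deaths.

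**Range.** With d from 1/10 to 1/20 per day and mortality pairs of 20/30%, 20/40% and 25/45%, the artificial difference in medians runs from 0.7 days (5.55 v 4.85) to 2.8 days (10.40 v 7.62).

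**Effect on a rank test.** Simulation: 1000 runs, 550 and 300 patients, two-sided 0.05, d = 1/15. Mann–Whitney rejects in 94% of runs on all patients and 80% on survivors only at 20% v 40% mortality. The figures are 38% and 30% at 20% v 30%, and about 5% for both when mortality is equal.

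**What a competing-event summary shows for the same patients at day 28.**
- Still in ICU: exp(−28/12) = 9.7% and exp(−28/9) = 4.5%.
- Dead in ICU: 0.20 × 0.903 = 18.1% and 0.40 × 0.955 = 38.2%.
- Discharged alive: 0.80 × 0.903 = 72.2% and 0.60 × 0.955 = 57.3%.

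Here the sicker group is correctly seen to leave the ICU alive less often.

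**ICU mortality if follow-up stopped at day 28.** Over the same range of assumptions, about 1–17% of a group would still be in the ICU, and ICU mortality would be understated by about 0.3–4 points per group. The difference between groups barely moves. The largest shift is at d = 1/20 with 20% v 30%, where 25.9 − 16.5 = 9.4 points instead of 10, a change of about 0.6.

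**The case against.** The strongest reply is that this is a condensed article without its analysis plan, and that how deaths enter a length-of-stay summary is commonly settled there. ICU times and vital status are collected, so a sound analysis remains possible. Read literally, the outcome is stay among patients transferred alive, which is usable as a description when ICU mortality stands beside it. This is why the point is a risk of bias and not a demonstrated bias. It does not remove the point, because the article itself fixes an end event that suits only survivors and then requires a comparison across severity grades.

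It is also fair that Section 2.10 never ties Mann–Whitney or the t-test to ICU stay, and that no comparison of stay by SIC status is spelled out. Only the test against SAC grade is explicit; a comparison by SIC status rests on the general wording about group comparisons.

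A reader might infer more from Section 2.18: that irreversible anonymization after day 28 destroys the ICU outcome of long-stay patients and so biases ICU mortality in the SIC comparisons. The documents do not support that. The sentence just before lets sites keep the key until data collection is complete, and ICU discharge status is a listed item for every patient. Under the assumed rates, a day-28 cut would change the group difference by only about 0.6 points, and mortality with a day-28 horizon is a separate outcome in the same subgroups. Nor is it shown that severe coagulopathy is over-represented among long stayers; in the illustration the higher-mortality group had fewer patients left at day 28 (4.5% v 9.7%).

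**Conclusion.** The point holds for ICU length of stay. The stated end event is unattainable for ICU deaths, the named methods do not handle death as a competing event, and the explicit comparison by SAC severity is one in which deaths are expected to differ. The size depends on rates the protocol does not give: 8.3 v 6.2 days in the central illustration, and 0.7–2.8 days over the range tried, with no true difference in discharge hazard. The illustration uses two groups and constant hazards, so it shows the mechanism and does not predict the study's result.

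The time limit is a minor point. ICU stay and ICU mortality are open-ended, and the two sentences in Section 2.18 point different ways for a patient still in the ICU at day 28. The day-28 clock starts at sepsis onset ("on the 28th day after sepsis onset, it will be determined whether cardiovascular events"), so the article states no follow-up end for patients without sepsis. This calls for clarification. Bias in the ICU-mortality comparison is not shown, and any effect is likely to be small.

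**What to change.** Redefine secondary outcome 1, in Sections 1.1 and 2.4 alike, as time to live ICU discharge:
- Use one time origin for all patients in a given comparison, for example sepsis onset in the SIC and SAC comparisons. Starting septic and non-septic patients at different points would make their stays non-comparable.
- Treat ICU death as a competing event and report the cumulative incidence of live discharge, with that of ICU death beside it.
- Also describe stay separately for patients discharged alive and those who died.

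For the minor point, state the time limit of ICU stay and ICU mortality, or state that they are open-ended. Reconcile the two sentences in Section 2.18 accordingly, and report how many patients were still in the ICU at day 28.

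The cost is slightly more analysis work, with no new data, since Section 2.5 already collects the dates and vital status. Recruitment has begun (Section 3.1.1), so the rule should be set before analysis. Amending the protocol text itself needs the approvals listed in Section 2.16.

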### 2.10. Statistical Methods

All patients who do not have SIC at the beginning of their individual observation period will be included in the calculation of the cumulative observation period for determining the incidence rate of SIC. The observation period for determining the incidence rate of SIC ends at the time of diagnosis of SIC or discharge from the ICU (depending on which event occurs first), but at the latest at the end of the 14-day observation period. The incidence rates for sepsis and septic shock are determined in the same way. To determine the incidence density, the number of incident patients is divided by the cumulative sum of the individual observation days of all patients included in the incidence calculation. The incidence density is thus calculated according to the following formula:$$\frac{\mathrm{Number}\;\mathrm{of}\;\mathrm{incidental}\;\mathrm{cases}}{\begin{array}{l} \mathrm{Sum}\;\mathrm{of}\;\mathrm{the}\;\mathrm{individual}\;\mathrm{observation}\;\mathrm{period}\;\mathrm{across}\;\mathrm{all}\;\mathrm{cases} \end{array}}$$

The corresponding 95% confidence interval is calculated based on a Poisson distribution. The incidence rates between the individual strata will be compared in pairs.

The point prevalences for SIC, sepsis, and septic shock will be determined on the first day of the observation period by calculating the ratio of the number of affected patients to the total number of patients in the ICUs on that day. The Wilson score method will be used to determine the associated 95% confidence interval. Using χ^2^ tests (or Fisher’s exact tests), the point prevalences of the individual strata will be compared. The prevalences of SIC, sepsis, and septic shock in the retrospective data collection will be determined analogously.

The available data will be described by specifying the median [interquartile range (IQR)] or the absolute (relative) frequency. Depending on the type of characteristic being analyzed, the different groups will be compared using the χ^2^ test (or Fisher’s exact test, if necessary), the Mann–Whitney U test, or the *t*-test. The Kaplan–Meier method will be used to determine survival times, and the log-rank test will be used for the relevant group comparisons.

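### Thromboembolism and bleeding are observed only to death, discharge or day 28, so comparing SIC/SAC groups by plain proportions mixes event rate with days at risk

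*Protocol article*

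**What the plan says.** **Observation window.** Section 2.4, outcome 5, reads "Thromboembolic events after sepsis onset (in sepsis, septic shock, SIC, or SAC (mild, moderate, severe)) up to day 28, death, or hospital discharge (whichever occurs"; the earliest of the three ends observation. Outcome 6, relevant bleeding, runs "until day 28, death, or hospital discharge (whichever occurs first". Both are listed by sepsis, septic shock, SIC and SAC grade.

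**Aim.** Section 2.5 says "it was decided to investigate the potential effects of SIC on thromboembolism and bleeding risk up to day 28". Section 1.1 adds, for SAC: "Each of the above-mentioned outcome parameters will also be tested for correlation with the different degrees of severity of SAC".

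**Recording.** Under Section 2.5, "until day 14 after the onset of sepsis, each patient will be checked for thromboembolic events" and major bleeding once a day. After that there is one entry at day 28: "yes/no recording for the second 14 days".

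**Analysis.** Section 2.10 describes categorical data by absolute and relative frequency. As a general rule, "the different groups will be compared using the χ^2^ test (or Fisher’s exact test, if necessary), the Mann–Whitney U test, or the *t*-test". Kaplan–Meier and log-rank are named for survival times, and the logistic models are for mortality and survival. Person-time denominators are given for the incidence rates of SIC, sepsis and septic shock, and for nothing else.

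**The concern.** The Introduction and the Discussion both state that SIC goes with higher morbidity and mortality. Patients with and without SIC are therefore likely to leave observation at different times. Earlier death shortens the time at risk in the SIC group. Earlier discharge shortens it in the non-SIC group, where events after discharge are not seen. A proportion with an event depends on both the daily event rate and the number of days watched, so a contrast between groups can come from either.

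The article says the study should inform trials of treatments that modulate coagulation. Differences in thrombosis and bleeding by SIC status or SAC grade are a natural input to such planning. A contrast produced by length of stay, or a real one masked by early deaths, would mislead it.

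**Working it through.** **Figures in the article.** It gives no event, death or discharge rates by SIC status, so there is no stated figure for these outcomes to reproduce. Its expected case numbers (Section 2.7) do reproduce:
- 6700 × 1500/12,000 = 837.5 sepsis patients, against about 850 stated.
- 0.30 to 0.60 × 850 = 255 to 510 SIC patients, against 250–500 stated.

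**Model (assumption).** Constant daily hazards for event *h*, death *d* and live discharge *x*, with *s* = *h* + *d* + *x*.
- Mean days at risk to day 28: *D* = (1 − exp(−28*s*))/*s*
- Proportion with an event: *P* = *h* × *D*

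**Inputs (all assumed).** *h* = 0.003 per day in both groups unless stated.

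| Case | Group | *d* | *x* | *s* | *D* (days) | *P* |
|---|---|---|---|---|---|---|
| a, b | non-SIC | 0.01 | 0.05 | 0.063 | (1 − 0.171)/0.063 = 13.15 | 3.95% |
| a | SIC | 0.02 | 0.02 | 0.043 | (1 − 0.300)/0.043 = 16.28 | 4.88% |
| b | SIC | 0.03 | 0.04 | 0.073 | (1 − 0.130)/0.073 = 11.92 | 3.58% |
| c | non-SIC | 0.01 | 0.03 | 0.043 | 16.28 | 4.88% |
| c | SIC | 0.04 | 0.04 | 0.083 | (1 − 0.098)/0.083 = 10.87 | 3.26% |
| c, *h* = 0.0045 in SIC | SIC | 0.04 | 0.04 | 0.0845 | (1 − 0.094)/0.0845 = 10.72 | 4.83% |

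**Observed risk ratios.**
- (a) 4.88/3.95 = 1.24, true hazard ratio 1.0
- (b) 3.58/3.95 = 0.91, true hazard ratio 1.0
- (c) 3.26/4.88 = 0.67, true hazard ratio 1.0
- (c) with a true hazard ratio of 1.5: 4.83/4.88 = 0.99

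Doubling *h* gives 1.23, 0.91, 0.67 and 0.98, so the assumed event rate hardly matters.

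**Events per day at risk.** *P*/*D* is 0.0030 in every group with *h* = 0.003, and 0.0483/10.72 = 0.0045 in the last row. The rate ratios are therefore the true 1.0 and 1.5.

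**When the distortion is smaller.**
- Events confined to days 0–7, other hazards unchanged: (a) 1.07, (b) 0.97, (c) 0.88. The true 1.5 in (c) appears as 1.31.
- Similar total exit: non-SIC 15% dead and 60% discharged by day 28, SIC 40% and 35%, event hazard 0.01 per day. A true 1.5 appears as 1.43.

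**Effect on the test.** With 850 patients, 30–60% SIC and *h* = 0.003, a two-sided 5% test of proportions rejects in about 9–11% of trials in (a), 5–6% in (b) and 17–23% in (c), although the event hazards are equal.

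**The case against.** **The test is inferred.** No sentence assigns a test to outcomes 5 and 6. It follows from a general rule that depends on the type of variable, and an unseen analysis plan may say more. This stands and limits the point to the method as stated. That method is still the only one in the article that fits these outcomes.

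**The proportion is valid.** Every patient is followed to day 28, death or discharge, so the proportion correctly estimates in-hospital cumulative incidence. A competing-risk curve ends at the same value on day 28, so drawing one does not change the comparison. This stands in full. A reader might infer that the planned proportions are wrong. They are not. The mismatch is between the proportions and the stated aim of an effect of SIC on risk to day 28.

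**The sizes are assumed.** This stands too. No hazards are given, and early clustering of events or similar exit rates shrink the distortion.

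**Reversal.** A reader might infer that a true increase could appear as a decrease. The cases shown above contain none. One can be constructed: a true 1.2-fold hazard appears as 0.77 if 50% of SIC patients die and 38% are discharged by day 28, against 15% and 45% without SIC. That is a strong contrast, and nothing in the article supports it.

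**A rate has its own trap.** SIC can start after sepsis onset. Rates counted from sepsis onset by whether SIC ever occurred would put pre-SIC days in the SIC denominator. This stands, and the fix must deal with it.

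**Conclusion.** The point holds in a limited form. The stated comparison of outcomes 5 and 6 describes in-hospital events correctly but cannot separate an effect of SIC from unequal days at risk. In the illustrations, no effect appears as a risk ratio of about 0.67 to 1.24, and a true 1.5-fold hazard can appear as about 1.0. Both rest on assumed constant hazards and on death and discharge rates that differ clearly by SIC status. The article supports only the direction of the mortality difference. The actual size and sign of any distortion cannot be known before the data are in.

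Only two secondary outcomes are touched. SIC incidence, prevalence and the 72-hour recovery rate are not affected by this point. It is worth correcting because the remedy is cheap.

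**What to change.** 1. Keep the proportions and label them *in-hospital events to day 28*, not 28-day risk.
2. For the SIC/SAC comparison, add events per 1000 in-hospital patient-days at risk over days 0–14, with a cause-specific rate or hazard ratio. The daily event checks, the date and time of hospital discharge and the status at discharge (Section 2.5) supply what is needed.
3. Treat SIC as time-updated from its registered first occurrence and the daily scores, or use a landmark day, so that pre-SIC days count as unexposed. Daily SIC scores stop at ICU discharge, so state how status is handled on the ward. INR and platelet counts are listed only for days 0–4 and the day of discharge, so a landmark may suit SAC grade better.
4. Show cumulative incidence with death and live discharge as competing events, as a description.

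**Cost.** A few lines in the analysis plan, some programming and no new data. The rate comparison covers days 0–14 only, because days 15–28 are recorded as yes/no. It removes the part due to time at risk and does not deal with confounding.
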